#### Concealed allocation

A computerised randomisation schedule stratified for site (Brisbane, Melbourne) will be prepared by an independent off-site body (The Berghofer Queensland Institute of Medical Research, Clinical Trial and Biostatistics Unit). To conceal randomisation, consecutively numbered, sealed, opaque envelopes will be prepared by a research assistant not involved in recruitment, and kept in a locked cabinet accessible only to the assistant. These envelopes will be opened at each site sequentially once the participant has been confirmed into the study by MRI, and all baseline measurements have been completed. If allocated into the CSI group, an appointment will be made for the participant to receive an US-guided injection, administered by an experienced Radiologist/Sports Physician. If allocated into the exercise and load management group or into the group that will adopt the wait and see approach, an appointment will be made for the participant to attend a trial physiotherapy clinic.

#### Blinding

The investigator assessing the outcome measures will be blind to group allocation, and will not be involved in any of the interventions. Participants will be informed in writing and verbally that they have an equal chance of being allocated into one of the three groups (CSI, exercise and load management, wait and see). They will not be made aware of the study hypotheses. Participants will be requested not to divulge any details about their treatment group to the investigator involved in assessing the outcome measures, and will be reminded of this prior to each encounter. It is not possible to blind the patients, physiotherapists providing the treatment, the radiologist administering the CSI, nor the physiotherapists providing the basic information to the wait and see group. Statistical analysis will be conducted on a blinded intention-to-treat basis.

#### Interventions

*Corticosteroid injection:* Participants allocated to this group will attend the clinic of the experienced radiologist or sports physician who will be performing the injection. Seven specialist radiologists are participating in this trial, with a range of 15–40 years of experience. The injection will be performed at the same radiology clinic that the participant attended to have their MRI and XRay investigations performed. After standard preparation procedures, the participant will be positioned on the table with the affected side raised. A preliminary ultrasound scan will be performed with pre procedural images taken in a longitudinal plane. The depth of injection required will be measured and area of maximal tenderness marked. A linear probe which is appropriate for the participant body habitus (i.e. 12 MHz) will be cleaned using sterile wipes, and the appropriate syringe and needle selected. A further preliminary scan will be performed, and the radiologist washes their hands and gloves up. The steroid (Celestone 1 ml or Kenacort A40 1 ml (depending on availability)) and local anaesthetic (Bupivacaine 2 ml or Marcaine 1 ml) will be drawn up using sterile techniques and the participant’s skin and ultrasound probe will be cleansed with chlorhexidine and the area draped. The radiologist will place the needle through the superficial structures until it reaches the bursa following which the steroid and local anaesthetic mixture will be injected widely in different directions through the bursa. On completion of the procedure, a dressing will be applied to the puncture site. A post procedural check will be performed, and a further explanation of what to expect and basic advice on tendon care will be given to the participant. A weekly diary will be completed, recording levels of pain and function and any adverse effects.

*Exercise, education and load management programme:* Participants allocated to this group will be prescribed a home exercise programme to be performed daily, which will be limited to four to six exercises (to optimise adherence), and should take no longer than 15–20 min to complete. Participants will also receive more specific and detailed advice and education on tendon care. This information will be delivered in hard copy handouts, verbal explanation and DVD. They will attend the physiotherapy clinic for individual supervised exercise sessions, and be treated by an experienced and registered musculoskeletal physiotherapist. Treating practitioners will have attended a training session outlining the study objectives and requirements, demonstrating the exercise protocol and progressions, as well as the detailed education material, and will be expected to be proficient in the intervention. They will also be provided with a detailed study manual for reference. The physiotherapy sessions will be once a week for the first 2 weeks, then twice a week for the next 6 weeks. The first session will be 1 h long, in order to perform detailed education and demonstration of the exercises. Successive sessions will be 30 min in duration, and include a brief interview and physical assessment to gauge the response to the exercise and load management program, modify or progress the home exercises, and supervise a twice weekly heavier loading exercise programme.

The exercises will include functional retraining, and targeted strengthening for the hip and thigh muscles, with a particular focus on the hip abductor muscles, and dynamic control of adduction during function. Exercise difficulty will be gradually increased as tolerated by the participant, in order to optimise improvements in muscle strength and function without significant aggravation of the participant’s pain. Difficulty level will be monitored with the Borg Scale [30] where warm up will be performed at a light level (Borg 11–12), functional retraining at a somewhat hard to hard level (Borg 13–15), and the slow heavy targeted strengthening moving from somewhat hard towards the hard to very hard level (14–17), depending on the participants response to loading. No change in pain over the greater trochanter will be acceptable during functional retraining, as this may indicate inadequate alignment control, and excessive compressive tendon loading. As the heavy slow strengthening exercises avoid tendon compression completely, a maximum of NRS 5/10 pain will be tolerated as long as this eases afterwards and does not result in increased pain levels that night or the next morning. Participants’ responses to the exercises will be closely monitored, and loading levels adjusted as required to prevent any increases in pain from week to week. Table 3 outlines the clinic and home based exercise protocols, and Figs. 1 and 2 show some examples of the prescribed exercises.

**Table 3 Tab3:** Exercise Dosage and Progressions

Stage	Exercise	Effort	Speed	Reps	Sets	Freq
Week 1- Familiarisation	*Low load activations*	Light	Slow onset	10	1–2	BD
	Static Abduction:		Hold 5–10 s			
	In supine lying	Light	Slow onset	3–5	1	BD
	In standing		Hold 5–15 s			
	*Pelvic Control during Functional Loading:*					daily
	Bridging	Light	Moderate	10	1	daily
	Double Leg Bridging					
	Functional Strengthening:	Light- SWH	Slow	10	1	
	Double leg squats					
	*Abductor Loading* via *Frontal Plane Movement:*	Light	Moderate	10 each	1	daily
	Sidestepping					
Week 2 – Early Loading & Movement Optimisation	*Low load activations*	Maintain as per week 1				
	Static Abduction:					
	*Pelvic Control during Functional Loading:*					
	Bridging:					
	Double leg bridging	Light	Slow	10	1	daily
	Single leg biased ex:	SWH	Slow	5	1	
	Offset bridging					
	Functional Strengthening:					
	Double leg squats	Light	Slow	10	1	daily
	Single leg biased ex:	SWH	Slow	5	1	
	Offset squat					
	*Abductor Loading* via *Frontal Plane Movement:*	Light	Moderate	15 each	1	daily
	Sidestepping					
Week 3–8 – Graduated Loading	*Low load activations*	Maintain as per week 1				
	Static Abduction:					
	*Pelvic Control during Functional Loading:*					
	Bridging:	Light	Slow	5	1	daily
	Double leg bridging					
	Single leg biased ex	SWH – Hard		5–10	2	daily
	Functional Strengthening:					
	Double leg squats	Light	Slow	5	1	
	Single leg biased ex	SWH - Hard		5–10	2	
	*Abductor Loading* via *Frontal Plane Movement:*					daily
	Sidestepping	Light	Moderate	10 each	1	
	Band Sideslides	SWH- Hard		5–10 each	1–2	
Week 3–8 – Graduated Loading; Sliding platform with spring resistance	All supervised by Physiotherapist in Clinic					
*Warm up*	*Abductor Loading* via *Frontal Plane Movement:*					
	Bilateral Abduction:					Twice weekly
	In upright	Light	Moderate	5 each way	1	
	In minisquat	Light	Moderate	5 each way	1	
*Higher level loading*	*Abductor Loading* via *Frontal Plane Movement:*					Twice weekly
	Bilateral Abduction:					
	In upright	SWH-VH	Slow	5–10 each way	1	
	In minisquat	SWH-VH	Slow	5–10 each way	1	
	*Pelvic Control during Functional Loading:*	Light - SWH	Moderate	5–10	1–2	Twice weekly
	Scooter					

Repetitions (Reps); Frequency (Freq); Effort based on Borg Scale (Borg, [30]); Somewhat Hard (SWH); Very Hard (VH); Speed: Slow = 3 s each movement phase – up/down/in/out; Moderate = 2 s each movement phase; Bi-daily (BD)

**Fig. 1 Fig1:**
[figure not shown]
Offset bridging exercise

**Fig. 2 Fig2:**
[figure not shown]
Spring resisted abduction on a sliding platform

Adherence to the exercise programme will be monitored by the physiotherapists and with the participants also completing a daily diary, outlining the exercises completed (number of sets and repetitions), any adverse responses and action taken. If any adverse event occurs during the treatment period, the participants will also be encouraged to report directly to their physiotherapist (e.g. worsening of pain, new symptoms or any injury). Any reports of adverse events will be recorded in the treatment notes and diary. The diary will be collected from the participant at the 8 week follow up assessment.

*Wait and see:* Participants allocated to adopt a wait and see approach will attend one session with a trial physiotherapist, where they will receive reassurance that the condition is likely to resolve over time, as well as advice regarding general tendon care and self-management. They will also receive a standard information pamphlet about the condition and basic self-management. The therapists will take time to answer any questions about adopting a wait and see approach to ensure the participant is confident that this is an appropriate and sensible approach to adopt. Participants in this group will complete a weekly diary, outlining any problems that may have been encountered related to the study.

### Outcome measures

A battery of primary and secondary outcome measures will be recorded. They are summarized in Table 4.

**Table 4 Tab4:** Primary and Secondary Outcome measures

Primary outcomes	Measurement	Baseline	4 weeks	8 weeks	12 weeks	26 weeks	52 weeks
Average Pain over the last week	11-point Pain Numeric Rating Scale (NRS), with terminal descriptors of 0 = ‘no pain’ and 10 = ‘worst pain possible’	√	√	√	√	√	√
Perceived overall change in condition of Hip	Global Rating of Change Scale		√	√	√	√	√
Secondary Outcomes	Measurement						
Global Impact of pain	Lateral Hip Pain Questionnaire	√	√	√	√	√	√
Function	Patient Specific Functional Scale	√	√	√	√	√	√
Quality of life	EuroQoL	√	√	√	√	√	√
Muscle strength	Static painfree abductor muscle strength	√		√			
Muscle Function	Active Lag Abductor Muscles	√		√			
Pain Catastrophising	Pain Catastophising Scale	√	√	√	√	√	√
Depression	PHQ-9	√	√	√	√	√	√
Pain and Function	VISA-G	√	√	√	√	√	√
Pain Self-Efficacy	Pain Self-Efficacy Questionnaire	√	√	√	√	√	√
Physical Activity Levels	Active Australia Survey	√	√	√	√	√	√
Economic Costs	OCC-Q	√				√	√

*EuroQoL* European quality of life questionnaire, *PHQ-9* patient health questionnaire-9; *OCC-Q* osteoarthritis costs and consequences questionnaires

#### Primary outcome measures

There are two primary outcome measures: (1) Global Rating of Change Score, and (2) Average Pain over the previous week.The Global Rating of Change Scale (GROC) is an 11-point scale in which the participant is asked to rate their perceived overall change in condition of their hip from the time that they began the study until the present, as Worse, No Change, or Better. If they indicate worse, the patient will then be asked *how much* worse on a five-point scale from Very Much Worse to Slightly Worse, and if they are better, they will be asked *how much* better on a five-point scale from Slightly Better to Very Much Better [31] (Fig. 3). Measuring patient perceived change using scales such as the GROC scale has previously been shown to be clinically relevant and a stable concept for interpreting meaningful improvements from an individual perspective [32].The average pain over the previous week is measured on an 11-point Pain Numeric Rating Scale (NRS), with terminal descriptors of 0 = ‘no pain’ and 10 = ‘worst pain possible’. The minimum important difference (MID) for the NRS has been found to be -1.5 points for musculoskeletal disorders [33].

**Fig. 3 Fig3:**
[figure not shown]
Primary Outcome Measure 1: Global Rating of Change Scale, modified from Kamper et al [31]

#### Secondary outcome measures

To ensure we have sufficient information regarding treatment responses there are a battery of secondary outcome measures: (1) Hip abductor muscle strength, (2) The VISA-G questionnaire, (3) the Patient Specific Functional Scale (PSFS), (4) the Pain Self-Efficacy Questionnaire, (5) The Pain Catastrophising Scale, (6) the Patient Health Questionnaire 9 (PHQ9),(7) the Active Australia survey, (8) EuroQoL (EQ-5D™) and (9) modified Osteoarthritis Costs and Consequences Questionnaire (OCC-Q).Hip abductor muscle strength will be measured with the participant in the supine position, with the tested leg extended and the hip at 10° abduction and 0° flexion, and the opposite leg flexed at the hip and knee. The pelvis will be stabilized with a seatbelt and towel, strapped to the plinth, and the participant will hold the side of the plinth with both hands. The centre of the dynamometer (Nicholas, Lafayett, IN47903 USA) will be positioned above the lateral malleolus of the fibula. Although such devices have been shown to have good to excellent reliability in different populations [34], a strap will be placed around the dynamometer and the plinth to stabilize the dynamometer and provide resistance to the abducting force, to eliminate the potential effect of examiner strength [35] (Fig. 4). The distance between the centre of the dynamometer and the most lateral aspect of the greater trochanter will be measured to calculate lever arm length. The supine position was adopted rather than side lying, as many people suffering from gluteal tendinopathy are unable to lie on the affected side due to pain. It has been found that the supine position also produces less measurement variation than the side lying position when testing hip abduction strength with a dynamometer [36]. Each participant will have one practice trial, followed by three experimental trials of hip abduction strength. To avoid pain aggravation, the participant will be asked to ramp up their force gradually, and then maintain a maximal contraction for 5 s. Peak force (Newtons) will be noted for each contraction, and the maximal value achieved over the three repetitions will be recorded. The distance between the greater trochanter and the mid-point of the dynamometer placement (proximal to the lateral malleolus) is then measured (m). Torque (Nm) is then calculated by the equation T = F (N) × D (m), and then standardized to body weight (Nm/kg). Standard verbal encouragement will be provided, with a consistent volume and level of enthusiasm. Fifteen seconds rest will be allowed between each contraction. A pain score will also be recorded for each repetition. This strength test has excellent test-retest reliability in our laboratory (ICC (95 % CI): 0.90 (0.83–0.95)).The VISA-G questionnaire is a self-reported, patient-specific tool for evaluating the severity of disability in people with gluteal tendinopathy, and is modelled on other VISA questionnaires previously developed for Achilles and patellar tendinopathies, that have been shown to be valid and reliable tools for establishing severity of tendinopathy [37, 38]. This questionnaire consists of 8 items, addressing pain and function at the present time. Scores range from 0 to 100, with higher scores indicating less pain and better function. The VISA-G demonstrates good reliability and validity [39], providing an objective method for measuring changes in the severity of disability of people with gluteal tendinopathy.The Patient Specific Functional Scale (PSFS) is a self-reported, patient-specific measure, designed to assess functional change in patients presenting with musculoskeletal disorders, and has been shown to be reliable, valid, and responsive to change in a number of musculoskeletal populations [40–42]. Patients are asked to identify three important activities they are unable to perform or are having difficulty with because of their problem. They are then asked to rate the current level of difficulty associated with each activity on an 11-point scale (where 0 is ‘unable to perform the activity’, and 10 is ‘able to perform at the same level as before the injury or problem’). Following intervention, the patients are then asked to rate the activities previously identified [43]. A total score is obtained by the sum of the activity scores, divided by the number of activities. Lower scores indicate greater functional difficulty. The MID has been found to be between 2.3 and 2.7 PSFS points in patients with musculoskeletal disorders of the lower extremity [33].The Pain Self-Efficacy Questionnaire (PSEQ) [44] is a ten-item questionnaire used to assess the confidence that people with chronic pain have in performing activities while in pain. It covers a range of functions, including household chores, socialising, work, as well as coping with pain without medication. It takes 2 min to complete, has a high completion rate, can be used in assessment, treatment planning, and outcome evaluation [44], and has been shown to be a reliable and valid measure [45]. Participants are requested to rate how confidently they can presently perform the activities described on a seven-point Likert scale, where 0 = not at all confident and 6 = completely confident. The total score ranges from 0 to 60, where higher scores reflect stronger self-efficacy beliefs.The Pain Catastrophising Scale is a 13-item self-report scale to measure pain catastrophising, and has been shown to be valid and reliable [46]. Participants are asked to reflect on past painful experiences and to indicate the degree to which they experienced each of 13 thoughts or feelings when experiencing pain, on 5-point scales with the end points (0) not at all and (4) all the time. The Pain Catastrophising Scale produces a total score, and three subscale scores assessing rumination, magnification and helplessness. The total score ranges from 0 to 52, with higher scores indicating higher levels of pain catastrophization. Pain catastrophising is said to relate to various levels of pain intensity reporting, physical disability and psychological disability in clinical and nonclinical populations.The Patient Health Questionnaire 9 (PHQ-9) is a brief self-report tool for screening, diagnosing, monitoring and measuring the severity of depression. The nine item questionnaire determines the frequency of depressive symptoms over the past 2 weeks, where PHQ-9 scores of 5, 10, 15 and 20 represent mild, moderate, moderately severe and severe depression. In addition to making criteria-based diagnoses of depressive disorders, the PHQ-9 has been shown to be a valid and reliable measure of depression severity, and its brevity makes it a useful clinical and research tool [47]The Active Australia Survey measures participation in leisure-time physical activity. The core questions apply to 1 week preceding completion of the survey, and consist of a short and reliable set of eight questions that can be easily implemented via telephone interviewing techniques or in face-to-face interviews. The Active Australia Survey has good reliability and validity and has been used in national surveys [48]. A number of different measures of participation in physical activity during the previous week can be obtained, including how many sessions of physical activity, total time and average time spent in each activity and ultimately the proportion of people who were doing sufficient activity to gain health benefits, or those who were sedentary.The EuroQoL (EQ-5D™) is a standardised instrument for use as a measure of health-related quality of life. It is applicable to a wide range of health conditions and treatments, and provides a simple descriptive profile, where the participant indicates in tick boxes which statements about mobility, personal care, usual activities, pain and anxiety/depression best describe their health status, as well as a single index value for health status. The participant is asked to grade their current level of function in each dimension into one of 3° of disability (severe, moderate or none), and each health state is ranked and transformed into a single score, called the utility. This utility score is an expression of the Quality Adjusted Life Years (QALY), and is commonly used to make evidence-based decisions in analyses of cost-effectiveness [49]. It is designed for self-completion by respondents and is cognitively simple, taking only a few minutes to complete.Economic costs data will be obtained from a modified version of the Osteoarthritis Costs and Consequences Questionnaire (OCC-Q). It is a self-administered questionnaire, which gives a broad representation of health care costs, and has been shown to be a feasible and valid method of capturing health care use and costs for patients with hip or knee pain compared with accessing administrative databases [50].

**Fig. 4 Fig4:**
[figure not shown]
Measurement of maximum static abductor muscle strength

### Other measures

Several other measures will be included to provide additional information about participants, such as demographic information collected at phone interview and the initial physical screen. Participants in the CSI and wait and see groups will keep a weekly diary throughout the initial 8 weeks to record any adverse events and any co-interventions, including pain related medication use. This same information is captured via the daily diary in the physiotherapy group.

In addition to these measures the opportunity presents to test two novel condition-specific measures: (1) the Lateral Hip Pain Questionnaire (LHPQ) and (2) the hip abduction lag.The LHPQ has been designed as a self-reported measure of pain and function with focus on issues specific to lateral hip pain sufferers. It has two primary subscales – one for Activities of Daily Living (ADL), and one for Sport. The ADL subscale encompasses questions related to pain (frequency, overall intensity, intensity for specific tasks, time to pain onset, and pain duration after sustained sitting), impact on function (overall and specific activities), and pain beliefs (fear of physical activity, and permanent impairment). The participant is asked to consider these aspects over the past week, and the total score ranges from 0 to 100, with higher scores indicating less pain and better function. The Sports subscale requires self-rating of pain (pain intensity while participating in sport, pain behaviour, time to pain onset) and impact on sporting participation. It is not completed if the participant does not compete in sport. Again, the time frame is considered over the past week, and the total score ranges from 0 to 100. The LHPQ is in a development phase, and will be tested alongside this main trial, and validated against information collected from other concurrent outcome measures (VISA-G) (Additional file 1).Active lag of hip abduction (Active -Passive discrepancy) will be measured with the participant in the side-lying position, with the lower leg against the table in approximately 45° of hip flexion and 90° of knee flexion. The upper leg will be supported on pillows in a neutral position in the sagittal plane, with 10° abduction in the frontal plane to avoid compressive loading of the ITB over the greater trochanter. Rotation of the pelvis will be avoided, and a rolled towel will be placed under the waist angle to achieve a neutral lumbo-pelvic position. The assessor will stand behind the patient to ensure the pelvis is maintained in the starting position, and also stabilise the pelvis with a hand over the lateral iliac crest. A plurimeter (Australasian Medical & Therapeutic Instruments) will be placed on the distal femur, 5 cm proximal to the lateral joint line. The participant will be requested to actively abduct the hip to the maximal position that they are comfortably capable of, and this position will be recorded. The assessor will then passively abduct the hip to its end of range, stabilising the pelvis and supporting the lower leg, and this position will be recorded. A trial of this active and passive abduction movement will be performed first in order to ensure correct technique (hip in neutral flexion/extension and rotation), then this will be repeated three times. The difference between passive and active range of hip abduction is recorded as the Active Lag for each repetition, and the average of the three trials will be recorded for analysis.

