The secondary objectives are to: compare an exercise and load management programme with CSI on outcomes including pain, function, hip abductor muscle strength, psychological measures, quality of life and physical activity levels; evaluate the effects of the two treatments compared to a wait and see approach on these outcomes; determine the cost-effectiveness of the two treatments at 52 weeks; compare the adverse events associated with both treatments.

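### In weeks 1–8 adverse events are solicited more intensively in the exercise arm than in the CSI arm, so the planned comparison between the two is open to ascertainment bias

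*Protocol article*

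**What the plan says.** The secondary objectives at the end of the Background include the aim to "compare the adverse events associated with both treatments". The two treatments are the exercise and load management programme and CSI.

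The Other measures section sets the diaries: "Participants in the CSI and wait and see groups will keep a weekly diary throughout the initial 8 weeks to record any adverse events", together with co-interventions and pain medication. Of the exercise arm it says "This same information is captured via the daily diary in the physiotherapy group".

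The Interventions section adds further routes for the exercise arm:

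- Supervised sessions run "once a week for the first 2 weeks, then twice a week for the next 6 weeks".
- Sessions after the first "include a brief interview and physical assessment to gauge the response to the exercise and load management program".
- If an adverse event occurs during treatment, "the participants will also be encouraged to report directly to their physiotherapist"; the examples given are worse pain, fresh symptoms and injury.
- Such reports go into the treatment notes as well as the diary, which is handed in at the 8-week assessment.

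For CSI, the same section describes one injection visit and a weekly diary of pain, function and adverse effects.

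The Adverse events section provides for participants and treating clinicians in any arm to report to the research assistant, with no time limit. The Procedure section gives all arms questionnaires to week 52 and states that all medication use and co-interventions will be recorded. Table 4 has no adverse-event item.

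**The concern.** An adverse-event comparison is interpretable only if an event of a given kind has a similar chance of being recorded in each arm. Here the protocol itself sets unequal solicitation for the two arms it intends to compare, yet describes the diary information as the same. If the plan is followed as written, treatment and intensity of ascertainment are confounded. An apparent excess of minor events with exercise could arise with no true difference, or a true excess with CSI could be masked. No later analysis can recover events that were never elicited.

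A second, distinct matter is what happens after week 8. Once the diaries stop, no scheduled instrument asks about adverse events in any arm, and only the cost questionnaire (OCC-Q) at 26 and 52 weeks bears on later co-interventions.

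**Working it through.** The plan states no figure for detection or expected event rates, so there is nothing to reproduce. The check is a count of recording occasions, then an illustration.

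**Step 1. Recording occasions in weeks 1–8** (from Interventions and Other measures)

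| | Exercise | CSI |
|---|---|---|
| Diary entries | daily: 8 × 7 = 56 | weekly: 8 × 1 = 8 |
| Treating-clinician visits | 2 × 1 + 6 × 2 = 14 | 1 (injection) |
| Visits with stated interview and physical assessment to gauge response | 14 − 1 = 13 | none stated |
| Encouraged to report to treating clinician | yes, with examples | not stated |
| Recorded in treatment notes as well as diary | yes | not stated |

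The ratio of diary entries is 56 / 8 = 7. This measures opportunities to record. It is not a ratio of detection probabilities, because a weekly entry can still cover all seven days.

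**Step 2. What might be counted.** Worse pain is a named example of an adverse event only in the exercise arm. The CSI diary is described as recording pain levels alongside adverse effects. The same flare could be entered as an event in one arm and as a pain score in the other. The diary forms are not shown, so this is a possibility only.

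**Step 3. Illustration of size (assumed values).** Recorded risk = true risk × capture probability. With the same true risk in both arms, the true risk cancels and the recorded ratio equals the ratio of capture probabilities.

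- Assumed true risk 20%. Capture 90% in exercise: 0.20 × 0.90 = 18%.
- Capture 75% in CSI: 0.20 × 0.75 = 15%; ratio 0.90 / 0.75 = 1.2.
- Capture 60% in CSI: 0.20 × 0.60 = 12%; ratio 0.90 / 0.60 = 1.5.
- Wider assumptions: 0.90 / 0.70 = 1.29; 0.90 / 0.50 = 1.80; 0.95 / 0.40 ≈ 2.37.
- Equal capture: ratio 1.00.

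Chance of a nominally significant excess in the exercise arm with no true difference (normal approximation, two-sided 5%, 67 × 0.85 ≈ 57 per arm, true risk 20%): about 8% for capture 0.90 v 0.70 and about 23% for 0.90 v 0.50. With all 67 per arm these become about 9% and 26%. Under equal capture the figure is nominally 2.5% in that direction.

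**Step 4. After week 8.** Diaries cover 8 of 52 weeks; 52 − 8 = 44 weeks (44 / 52 = 85%) have no diary. This holds in all arms, so it bears on completeness and not on balance.

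**The case against.** The strongest reply is that more recording occasions need not mean more events detected. A weekly diary covers the whole week, the CSI diary tracks pain and function too, and the pain scale and global rating are collected identically in all arms at each follow-up. The comparison is also an unpowered secondary objective. All of this is fair, and it is why no size can be asserted. It does not remove the difference in clinician contact, prompting and recording.

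Several stronger statements that a reader might infer are not supported:

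- That capture stops at week 8. Only the diaries stop. The Adverse events section leaves spontaneous reporting open in every arm, so it is not established that late events are missed. That route does not fully offset the imbalance, because it relies partly on treating clinicians, who see exercise participants far more often.
- That CSI and wait-and-see participants have no contact after one visit. All arms have questionnaires, telephone or email contact and an 8-week reassessment.
- That therapists ask about adverse events at each of 14 sessions. The text describes an interview about response to the programme after the first session, and encouragement to report.
- That the wait-and-see diary omits adverse events. Interventions describes it more narrowly, as problems related to the study, but Other measures says it records any adverse events. That arm is also outside the stated comparison.

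It may also be said that diary wording and the pooling of sources belong in the full protocol or analysis plan. That is true of the detail, but the article itself fixes the unequal instruments.

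**Conclusion.** The point holds in a limited form. Solicited adverse-event capture in weeks 1–8 is more intensive for exercise than for CSI, and the protocol plans to compare events between these two arms. The comparison is therefore open to ascertainment bias. The probable direction is against exercise, on the assumption that more contact and prompting raise the recording of minor events. It would go too far to say that the comparison is shown to be biased, or that it cannot address the objective: the documents give no detection rates, so neither size nor direction can be proved. The ratio of 1.2–1.5 is conditional on assumed capture of 90% v 60–75% at equal true risk.

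The end of the diaries at week 8 is common to all arms. It leaves later adverse events to spontaneous reports and later co-interventions to the OCC-Q, which sits uneasily with the statement in Procedure that all will be recorded. It is a limit on completeness, separate from the imbalance. It does not touch the 52-week primary outcomes, which are measured in the same way in every arm.

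**What to change.** Add to the common questionnaires at 4, 8, 12, 26 and 52 weeks, in all three arms, one identical adverse-event question and one identical co-intervention and medication question, each with the same recall period across arms. Name these items as the basis for the between-arm adverse-event comparison. List diary and therapist-elicited events separately and descriptively, without comparing rates. Amend the sentence in Other measures so that it does not imply equivalent capture.

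The cost is about a minute of participant time per questionnaire and an ethics notification. The Availability section says the trial is in progress, so the items may reach only the remaining time points. Common capture would then be incomplete for participants already past the early visits. For them the week 1–8 comparison should be reported descriptively, with the unequal ascertainment stated as a limitation.
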